### Sample size

Currently, the overall incidence of Tic Disorder (TD) is approximately 1%. Based on preliminary test results from our research group [21], the average effectiveness rate of the acupuncture intervention group is 95%, while that of the control group is 55%. Accounting for a dropout rate of 20%, a total of 60 cases, with 30 cases in each group, were determined using the sample size calculation formula.

### Randomization

The subjects will be randomly assigned to two groups: the experimental group and the control group. There will be 30 cases in each group. Randomization was performed using the R software, generating a random number table with a block length of 4 and a distribution ratio of 1:1. Upon enrollment of eligible subjects, the randomizer allocated them to groups based on the order of their entry into the trial, labeling “1” as the experimental group and “2” as the control group. Throughout the trial, the acupuncturist will be aware of the patient’s group allocation. The subjects, evaluators of therapeutic effects, and individuals conducting the statistical analysts will be blinded to group allocation.

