## Materials and methods

### Study design and participants

This is a randomized controlled trial, recruiting a total of 90 children (30 healthy children and 60 children with TD) in the outpatient department of acupuncture and rehabilitation department of Affiliated Hospital of Nanjing University of Traditional Chinese Medicine, in which they will be divided into non-intervention group and intervention group. The non-intervention group consists of 30 healthy children while the intervention group consists of 60 children with TD. The intervention group will be randomly allocated into either the treatment group or the control group, with 30 children randomly assigned in each group. Participants with tic disorder will also be recruited through posters and official WeChat accounts. The researchers will use the American Psychiatric Association DSM-5 criteria for tic disorder to assign a diagnosis. Individuals who meet the inclusion criteria will receive free complimentary clinical testing and some treatment subsidies to encourage enrollment. The details of the clinical trial and the collection of samples will be explained to the parents of the patients before obtaining their written consent. This research was approved by the Ethics Committee of the Affiliated Hospital of Nanjing University of Traditional Chinese Medicine (Jiangsu Provincial Hospital of Traditional Chinese Medicine) (2023NL-095-02), and the trial has been registered in China Clinical Trial Registration Center(ChiCTR2300075188).The flow of the trial is presented in Fig. 4. The schedule of the trial is shown in Table 1.

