## Intervention

To ensure optimal therapeutic outcomes, all acupuncture treatments are conducted by a qualified acupuncturist with over 3 years of clinical experiences. Prior to the trial, the acupuncturist undergoes specialized training on the treatment process and adheres to standardized acupuncture protocols.

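### One fixed, published block length of 4 lets anyone who holds the ordered allocation history know, on average, a third of the assignments before entry

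*Protocol article*

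**What the plan says.** The Randomization section of the protocol article states a single block length, 4, at 1:1 ("generating a random number table with a block length of 4 and a distribution ratio of 1:1"). Assignment runs down one sequence: "the randomizer allocated them to groups based on the order of their entry into the trial". No stratification and no variation in block length are mentioned. The same section says "Throughout the trial, the acupuncturist will be aware of the patient’s group allocation", while children, outcome evaluators and statisticians are to be blinded.

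The Intervention section says "all acupuncture treatments are conducted by a qualified acupuncturist with over 3 years of clinical experiences". Study design and participants places recruitment "in the outpatient department of acupuncture and rehabilitation department" of one hospital, with further recruitment by posters and WeChat. The Sample size section gives 60 randomised children, 30 per group. Case criteria dates the start to September 2023 and expects completion by December 2025. Trial status says recruitment is still under way.

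**The concern.** In a permuted block of known, constant length, the later places are fixed by the earlier ones. Once two children in a block of 4 have gone to one arm, the rest of that block is known. Concealing the list, or giving it to a separate randomizer, does not prevent this, because the prediction uses only past assignments and the block length. Here the length is in print and at least one role in the recruiting department is unblinded.

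What is at stake is the randomised YGTSS comparison. If someone who can foresee the next arm also affects which child is entered, or in what order, the arms may differ in prognosis at baseline. Blinding children and raters acts after entry and does not undo that. Analysis can repair it only in part.

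**Working it through.** **Inputs.** Block length 4, ratio 1:1, order of entry (Randomization); 60 children, 30 per group (Sample size). Assumption: the observer knows all earlier assignments in order, and so knows where each block starts. The article gives no predictability figure to reproduce.

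**Consistency of the plan's own figures.** 60 / 4 = 15 complete blocks, and 15 × 2 = 30 per arm, as stated.

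**Certain assignments.** With E for experimental and C for control, a block has six equally likely orders: EECC, ECEC, ECCE, CEEC, CECE, CCEE.
- Places 1 and 2 are never certain.
- Place 3 is certain when the first two match (EECC, CCEE): 2/6 = 1/3.
- Place 4 is always certain.

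Expected per block: 0 + 0 + 1/3 + 1 = 4/3, and (4/3) / 4 = 33.3%. Over 15 blocks: 15 × 4/3 = 20 of 60. Each block contributes one or two certain places, so the total lies between 15 and 30, with SD √(15 × 1/3 × 2/3) = 1.8.

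**Best guess.** Probability of a correct guess by place:
- place 1: 1/2
- place 2: 2/3
- place 3: 1/3 × 1 + 2/3 × 1/2 = 2/3
- place 4: 1

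The sum is 17/6 = 2.833 per block, and 2.833 / 4 = 70.8%, or 15 × 17/6 = 42.5 of 60. Simple randomisation gives 50%, or 30 of 60.

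**Varied block sizes.** These come from 4,000 simulated lists of 60 with each size equally likely. The observer knows the set of sizes and updates optimally after each assignment. That favours the observer, who would know less if the sizes were undisclosed.

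| Block sizes | Certain | Correct guesses |
|---|---|---|
| 4 (plan, exact) | 33.3% | 70.8% |
| 2, 4 | 10.9% | 72.1% |
| 4, 6 | 5.5% | 69.0% |
| 2, 4, 6 | 4.0% | 70.1% |
| 4, 6, 8 | 2.3% | 67.8% |

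In the last three rows, certain assignments fall from 20 of 60 to between 1.4 (0.023 × 60) and 3.3 (0.055 × 60). The excess of right over wrong guesses, 2p − 1, moves much less: from 2 × 0.708 − 1 = 0.42 to between 2 × 0.678 − 1 = 0.36 and 2 × 0.701 − 1 = 0.40.

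**The case against.** The arithmetic is not in dispute. The objection is that predictability harms the trial only if one person both holds the ordered history and affects entry, and the article does not describe such a person.

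- It says that the researchers make the diagnosis, that a randomizer assigns, and that assignment follows enrolment. Table 1 puts screening and consent at Week -1 and allocation at Week 0, which leaves less room to act on a guess after consent.
- The sentence on a qualified acupuncturist can be read as a qualification requirement and not as a headcount. With 60 × 36 = 2,160 sessions, treatment may be shared, and then no one person need see the whole sequence.
- A condensed article may leave enrolment roles to the full protocol.
- On the 2p − 1 measure, varying the block size gains little.

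Most of this stands. A reader might infer that the acupuncturist selects children, or that the YGTSS comparison is biased by some number of standard deviations. The document supports neither. No passage gives the acupuncturist a part in screening or entry. Putting the bias in standard deviations would need an assumed prognostic difference between children entered under opposite guesses, and the article offers no source for one. The limited gain in guess rate is also real.

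What the objection does not remove is the stated method itself: a fixed length, published during recruitment, with an unblinded provider. That is a choice the article makes, not a detail it omits, and fuller concealment steps elsewhere would not change the one-third figure.

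**Conclusion.** The point holds as a modest, avoidable design weakness. To anyone who knows the ordered history, one third of assignments are certain on average (20 of 60, range 15 to 30) and 70.8% can be guessed. These figures are exact for blocks of 4 at 1:1. They rest on that person tracking every assignment in a single unstratified sequence. Whether selection bias follows depends on influence over entry, on which the article is silent. The 20 of 60 covers the whole trial; the number still to be randomised, which is all a change can reach, is not given.

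A reader might also infer that the published 1/2 group code would unblind the statisticians. The document does not support this. It uses the code for the allocation list, says that "individuals conducting the statistical analysts will be blinded to group allocation", and nowhere says that the analysis data will carry the same labels.

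**What to change.** Generate the allocations not yet used with randomly varied block sizes, for example 4, 6 and 8, and do not disclose the sizes until recruitment closes. Avoid a 2/4 mix, which leaves 10.9% certain and raises the guess rate to 72.1%. Because varied sizes remove certainty but not most of the predictability, also keep the treating acupuncturist out of screening and out of the order of entry, and say so in the protocol. If the full protocol already separates these roles, a reference to it is enough.

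The cost is a few lines of R and a protocol note. The arms may also end slightly unequal. If the block of 4 in progress is completed first and entry stops at 60 inside a block of 8, the arms can differ by at most 8 / 2 = 4 children, that is 32:28.

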## Intervention

To ensure optimal therapeutic outcomes, all acupuncture treatments are conducted by a qualified acupuncturist with over 3 years of clinical experiences. Prior to the trial, the acupuncturist undergoes specialized training on the treatment process and adheres to standardized acupuncture protocols.

### Behavior therapy

Psychological counseling is provided to children and their families, offering information about the disease and assisting in developing a proper understanding of Tic Disorder (TD). The importance of a nurturing living environment and harmonious interpersonal relationships for the child’s recovery is emphasized. Encouraging children to engage in communication with their peers helps alleviate any inferiority complexes that they may have, while guiding them to actively participate in creative activities which aims to divert their attention and reduce the occurrence of TD symptoms, thus facilitating their rehabilitation. Additionally, families are advised to plan a healthy balanced diet and creating a well-structured routine to ensure consistency and alleviate academic pressures on children [22].

### Acupuncture needles

Acupuncture needle: The disposable stainless steel acupuncture needle used in this study is the “Huatuo” brand, with dimensions of 0.30 mm in diameter and 25 mm in length, manufactured by Suzhou Medical Supplies Factory.

Sham acupuncture device: The PSD + retractable blunt needle, a disposable stainless steel sterile blunt needle imported from Britain and produced by Acu Prime brand, was employed in this study. The selected specifications for this needle are 0.30 mm in diameter and 25 mm in length. It is authorized by Dong Bang Acupuncture Company, with approval number 9,018,390,000. (Fig. 5)

**Fig. 5 Fig5:**
[figure not shown]
Sham acupuncture needles

### The experimental group

The experimental group received a combination of acupuncture therapy and behavioral therapy. The acupuncture protocol consisted of targeting specific acupoints including Baihui, Yintang, Dazhui, Ganshu, Hegu, Zusanli, Sanyinjiao, and Taichong. For the precise location of these acupoints, please refer to Table 2; Fig. 6.

**Table 2 Tab2:** The precise location of the acupoints

Acupuncture points	Description
GV20: Baihui	On the head, 5 B-cun superior to the anterior hairline, on the anterior median line.
EX-HN3: Yintang	On the forehead, at the midpoint between bilateral eyebrows.
GV14: Dazhui	In the posterior region of the neck, in the depression inferior to the spinous process of the seventh cervical vertebra (C7), on the posterior median line.
BL18: Ganshu	In the upper back region, at the same level as the inferior border of the spinous process of the ninth thoracic vertebra (T9), 1.5 B-cun lateral to the posterior median line.
LI4: Hegu	On the dorsum of the hand, radial to the midpoint of the second metacarpal bone.
LR3: Taichong	On the dorsum of the foot, between the first and second metatarsal bones, in the depression distal to the junction of the bases of the two bones, over the dorsalis pedis artery.
ST36: Zusanli	On the anterior aspect of the leg, on the line connecting ST35 with ST41, 3 B-cun inferior to ST35.
SP6: Sanyinjiao	On the tibial aspect of the leg, posteriorto the medial border of the tibia, 3 B-cun superior to the prominence of the medial malleolus.

**Fig. 6 Fig6:**
[figure not shown]
Acupuncture point. The accurate positioning of acupuncture points

The therapeutic needle selected for this study is the disposable stainless-steel needle (0.30 mm in diameter and 25 mm in length), produced by the “Huatuo” brand of Suzhou Medical Supplies Factory. Following routine skin disinfection, the acupuncture angle and depth will be adjusted based on the specific requirements of each acupoint. Subsequently, the electroacupuncture device is connected to both sides of Hegu and Taichong; as on head Baihui and Yintang is connected as a pair, by utilizing a continuous wave frequency at a voltage in which the child can tolerate. Participants will receive three 30-minutes acupuncture sessions per week for a total of 12 weeks.

### The control group

This group received a combination of sham acupuncture and behavioral therapy, and the acupuncture points selected are the same as used in the experimental group. Remove the apron on the skin surface of a PSD base, introduce a disposable blunt needle, expose the needle tip, stick it on the acupoint. Since the blunt needle will retract back into the hollow handle of the needle when it touches the skin, it will not penetrate through the skin and so the needles will just appear to be floating on the skin surface. Acupuncture manipulation, electroacupuncture treatment, treatment duration and period are the same as those in the experimental group.

All acupuncture treatments conform to the Report Standard of Intervention Measures in Acupuncture Clinical Trials [23], refer to supplement 2.

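### The control arm is described as a non-penetrating sham that nevertheless receives the same manipulation and electroacupuncture at the same points, so what the trial contrasts is unclear and masking of child and guardian is not supported

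*Protocol article*

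**What the plan says.** Four parts of the protocol article bear on this.

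- **The control group.** "the acupuncture points selected are the same as used in the experimental group". The sham is set up thus: "Remove the apron on the skin surface of a PSD base, introduce a disposable blunt needle". Because the needle retracts on contact, "it will not penetrate through the skin and so the needles will just appear to be floating on the skin surface". The section then says: "Acupuncture manipulation, electroacupuncture treatment, treatment duration and period are the same as those in the experimental group".
- **The experimental group (text after Fig. 6).** Needles are inserted: "the acupuncture angle and depth will be adjusted based on the specific requirements of each acupoint". Then "the electroacupuncture device is connected to both sides of Hegu and Taichong", with Baihui and Yintang joined as a further pair, at a voltage the child can tolerate. No adhesive base is mentioned.
- **Acupuncture needles.** The two needles come from different makers. The sham needle has the same dimensions as the real one: "The selected specifications for this needle are 0.30 mm in diameter and 25 mm in length".
- **Randomization.** The acupuncturist knows the allocation. "The subjects, evaluators of therapeutic effects, and individuals conducting the statistical analysts will be blinded to group allocation". Guardians are not named.

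Under Primary outcomes, the YGTSS is scored by a clinician who questions the guardians and observes the child.

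**The concern.** What the control arm receives decides what the randomized comparison estimates, and no later analysis can repair it. The text specifies a needle that stays outside the skin, and then declares manipulation and electrical treatment equal to those given through needles placed at a chosen angle and depth. Nothing says that current in the control arm is off, reduced or disconnected.

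If the statement is followed as written, the control is not inert. The Abstract and Introduction nonetheless frame the result, for symptoms, thermography and metabolomics alike, as evidence on acupuncture and its mechanism. If the statement is not meant literally, the two arms feel different in a trial that claims masked participants, and the primary score depends partly on what guardians report.

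**Working it through.** **Step 1. Compare the arms as described.**

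| Feature | Experimental | Control |
|---|---|---|
| Acupoints | Eight named points | Same points |
| Needle size | 0.30 mm × 25 mm | 0.30 mm × 25 mm |
| Penetration | Yes, depth set by point | None; needle retracts |
| Adhesive base | Not mentioned | Described |
| Manipulation | Through an inserted needle | Stated to be the same |
| Current | Hegu, Taichong, Baihui–Yintang, tolerable voltage | Stated to be the same |
| Sessions | 3 per week × 12 weeks = 36 | Stated to be the same |

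The manipulation and current rows do not fit the penetration row. Manipulating a needle that rests on the skin is not the same procedure as manipulating an inserted one, and current applied at the skin surface is not the same as current applied through an inserted needle.

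**Step 2. Take the two readings separately.**

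- *Current is delivered to controls.* Both arms get electrical stimulation at the same points. The arms differ in penetration, and the trial estimates what penetration adds to surface stimulation. Electrical sensation is shared, which helps masking.
- *Current is not delivered.* The control is closer to inert and the contrast closer to the stated one. The equality sentence is then false, and electrical sensation occurs in one arm only, which works against masking of the child.

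Dilution of the effect belongs to the first reading and unequal sensation to the second. They cannot both apply. The base, described for one arm only, and the omission of guardians from the blinding statement stand under either reading.

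**Step 3. Reproduce the planned sample size.** Inputs from Sample size: 95% versus 55%, 20% dropout, 60 in total. The two-sided 5% level is taken from Statistical analysis. Power is not stated, so it is an assumption. The pooled formula is

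n = [1.96·√(2·p̄(1−p̄)) + z·√(p₁(1−p₁) + p₂(1−p₂))]² / (p₁−p₂)², with p̄ = 0.75.

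- At 90% power: [1.96·0.6124 + 1.2816·0.5431]² / 0.16 = 22.5, so 23 per arm; 23/0.80 = 28.75, so 29 per arm and 58 in total, close to the stated 60.
- At 80% power: 18 per arm, 23 after dropout, 46 in total.

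**Step 4. Illustrate the cost of an active sham (first reading only).** Evaluable per arm: 30 × 0.80 = 24. Suppose the sham produces a fraction f of the 40-point difference, so that the control rate is 55% + f × 40%. The fractions are assumptions; the document gives none.

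Power = Φ{[(p₁−p₂)·√24 − 1.96·√(2p̄(1−p̄))] / √(p₁(1−p₁) + p₂(1−p₂))}

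- f = 0: control 55%; (0.40·4.899 − 1.96·0.6124)/0.5431 = 1.40; power 92%.
- f = 0.30: control 67%; (0.28·4.899 − 1.96·0.5548)/0.5183 = 0.55; power 71%.
- f = 0.50: control 75%; (0.20·4.899 − 1.96·0.5050)/0.4848 = −0.02; power 49%.

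**The case against.** A non-penetrating sham at the same points is openly described and is a legitimate design choice. The article is condensed; it refers to a supplement on intervention reporting and to a picture of the sham needle, neither of which is shown here. Silence about a base in the experimental arm does not prove that none is used. Needle dimensions are matched. In a parallel-group trial each child, as described, meets only one device, two of the points (Dazhui and Ganshu) lie on the neck and back out of the child's sight, and nothing says that guardians watch the sessions. Evaluators and analysts can stay blinded whatever the needle looks like.

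Most of this stands. A reader might infer that the devices are visibly different and that the blinding claim therefore fails. The documents do not support that: the appearance of the devices is not shown, and a risk to masking is not evidence of its loss. A reader might also charge the plan with dilution and unequal sensation together, but these arise under opposite readings.

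What the objection does not remove is the equality sentence. It is a positive statement, not an omission, and it conflicts with the description of the needle just before it. Nor does a blinded rater protect against bias that enters through a guardian who has formed a view of the allocation.

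**Conclusion.** The point holds in a limited form. The description of the control arm is internally inconsistent. Followed as written, it gives controls electrical stimulation at the therapeutic points, and the trial then cannot support a conclusion about acupuncture against an inactive sham. If no current is given, the sentence misstates the control and the arms differ in electrical sensation. In both cases, masking of child and guardian is at risk and unsupported by the description, but not shown to fail.

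The size cannot be fixed from the document. The drop in power from 92% to about 71% or 49% is illustrative: it applies only if current is delivered, it rests on assumed fractions of 30% and 50%, and it takes the planned rates and dropout at face value. The article does not say what treatment lay behind the 55% control rate, so that rate may already include some effect of a sham. The main consequence is for what the comparison means. Which form of stimulation is appropriate in the control arm is not judged here.

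**What to change.** 1. Reconcile the sections on randomization, needles, the experimental group and the control group on three facts: whether current is delivered in the control arm, what equal manipulation means for a needle that retracts, and whether both arms use the same base.
2. If current is delivered, restate the trial question and the planned conclusion as the effect of needle penetration over surface stimulation at the same points. If it is not, correct the equality sentence and limit the claim of participant blinding accordingly.
3. State whether guardians are meant to be blinded, since they inform the YGTSS.
4. Record a treatment guess from child and guardian at week 12 and report it beside the YGTSS result.

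The cost is amendment wording and one extra question; no more children are needed. Because recruitment is under way, children who have already finished will have no recorded guess, and this should be reported. These steps document what is delivered and do not ask for a change of device or treatment delivery during the trial.
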